## Abstract

The relationship between multiple sclerosis (MS) and females is a crucial aspect in the development of the disease, with the ovarian hormonal cycle being a sensitive stage, especially in females with relapsing-remitting multiple sclerosis. The objectives of the study are to identify moderating variables that modify satisfaction with physical activity practice throughout the menstrual cycle (MC) in females in or out of their MC, during high-intensity interval training (HIIT) and strength training sessions and to compare the acute effects of different types of physical activity sessions in females with and without MS. This protocol is the methodology used in the EMMA Study, a randomised, single-blind crossover trial study conducted in females with MS who were matched 1:1, based on age, lifestyle factors and country of residence, with females without MS, to analyse the effect of physical activity practice on satisfaction, functionality, fatigue and inflammatory profile through their MC. Participants will visit the facilities approximately 10 times (4 preliminary familiarisation visits and 6 visits to carry out a physical activity session in each phase of the MC) for 3–4 months. A total sample of 30 females (15 females without MS and 15 with MS) is necessary for the study. The evaluation will comprise clinical, nutritional and psychological interviews, including different variables. It is hypothesised during the luteal phase, females with MS are expected to exhibit different acute responses to HIIT and strength training sessions as compared with females without the disease. Before starting the study, all participants will read and sign an informed consent form. Trial registration number: This research protocol is registered with ClinicalTrials.gov to ensure transparency and accessibility of study information (NCT06105463). The university’s ethics committee number for this study is UALBIO2022/048.

WHAT IS ALREADY KNOWN ON THIS TOPICMultiple sclerosis (MS) predominantly affects females and exhibits a complex relationship with the menstrual cycle. Hormonal fluctuations during the menstrual cycle have been linked to changes in MS symptoms, but the acute responses to physical activity in different menstrual cycle phases are not well understood. Existing knowledge emphasises the importance of gender and hormonal factors in the clinical management of MS.WHAT THIS STUDY ADDSThis study, part of the EMMA Project, aims to investigate how satisfaction with physical activity varies throughout the menstrual cycle in females with and without MS. It also explores the acute effects of different physical activity sessions (high-intensity interval training and strength training). The study examines hormonal, functional and psychological aspects, shedding light on the interplay between MS, gender and the menstrual cycle, with implications for tailoring exercise regimens for individuals with MS.HOW THIS STUDY MIGHT AFFECT RESEARCH, PRACTICE OR POLICYThe EMMA Study can contribute to more personalised exercise programmes for females with MS by considering their menstrual cycle phase. The findings may provide insights into the role of hormonal fluctuations in symptom exacerbation and the effects of high-intensity interval training and strength training. This knowledge could enhance MS management strategies, emphasising gender-specific approaches and optimising outcomes for individuals with MS. The study’s results are expected to have significant implications for research, practice and policy, contributing to a better understanding of how the menstrual cycle affects the acute response to exercise in females with MS.

## Introduction

Multiple sclerosis (MS) is one of the most prevalent neurological diseases that affect young adults, typically occurring in individuals aged between 20 and 40 years old, with a higher incidence in females, in a ratio of approximately 2.3:3.5.^1^ The total prevalence is 33 cases per 100 000 people,^2^ affecting more than 2 million individuals worldwide.^3^ Interestingly, the global incidence and prevalence of MS are increasing, even in regions previously considered to be low risk.^4^ This chronic disease significantly affects individuals, leading to disability and impairment, making their personal, social and occupational lives very challenging.^5^

Although the aetiology of MS is unknown, it is believed to be a multifactorial disease resulting from the interaction of genetic, infectious and environmental factors (such as smoking, the ubiquitous γ-herpes virus, vitamin D deficit and exposure to sunlight).^6^ These factors, along with hormonal influences, contribute to the sexual differences observed in MS.^7^ Females experience more frequent relapses in relapsing-remitting MS (RRMS). They also develop more inflammatory lesions and have an earlier onset.^1^ Furthermore, the age of menarche is inversely associated with the risk of MS, and a lower relapse rate has been observed during pregnancy and menopause. In comparison, a higher relapse rate occurs after delivery.^8^ These findings highlight the importance of sex-specific approaches in the clinical management of MS, suggesting meaningful connections between gender, hormonal status and disease progression.

More specifically, menstruating females with MS during their premenstrual phase, and especially those with RRMS, could experience a worsening of symptoms due to exacerbation (new demyelinating plaques) and pseudoexacerbation (worsening of pre-existing deficits due to previous plaques).^7^ Additionally, body temperature fluctuates during the menstrual cycle (MC), increasing shortly after ovulation and remaining elevated throughout the luteal phase.^9^ This temperature increase can lead to the Uhthoff phenomenon, a temporary worsening or exacerbation of neurological symptoms due to heat.^7^ Furthermore, hormonal changes during the MC also moderate symptom fluctuations in females with MS.^9^

The long-term immunomodulatory effect of exercise is well-known. It has been shown that it can lead to a reduction in inflammation^10^ and the partial regulation of neuroimmune parameters in T cell behaviour.^11^ On the other hand, in healthy females, it has been observed that during physical activity (PA), hormonal fluctuations also lead to differences in performance and muscle damage. The perception of delayed-onset muscle soreness (DOMS) and loss of strength in response to PA is lower during the luteal phase when sex hormone concentrations are high. At the same time, during the early follicular phase (EFP), a greater perception of DOMS and a more significant loss of strength are observed.^12^ In this sense, the acute effects of exercise lead to an increase in T cell subsets 30 min after completing PA, followed by a decrease between 1 and 2 hours in healthy females. Training intensity modifies the immunomodulatory effect of T cell subpopulations and cytokines in healthy populations, generating a chronic response to immune system impairment.^13^ Therefore, PA could induce acute adverse events in females with MS during their reproductive years, especially during some phases of the MC, due to temperature changes and the acute inflammatory response to PA. However, to date, the acute response to exercise in females with MS and its relationship with hormonal fluctuations is still unclear.

Exercise has been proposed as a potential approach to improve MS symptoms, with aerobic exercise and strength training being the most commonly used and effective exercise modalities within the female population. Furthermore, it is worth noting that high-intensity interval training (HIIT) shows promise in enhancing fitness outcomes for individuals with MS.^14^ In this context, HIIT and strength training emerge as promising exercise strategies. However, achieving substantial benefits requires a minimum number of exercise sessions, underscoring the importance of adherence to the exercise programme when demonstrating positive effects.^15 16^ While the exact dropout and adherence rates in exercise programmes for MS remain unclear, several factors, such as age, gender distribution, disability level, exercise modality (HIIT vs strength training), intervention duration and specific exercises included, could potentially influence the dropout rate in physical exercise programmes.^17^ Hence, studying satisfaction with practising these exercises following a session is crucial. Understanding patients’ experiences and satisfaction levels can contribute to designing more effective and sustainable exercise programmes for those living with MS.

Even though age and gender are key factors that influence adherence and optimising outcomes, studies on MS and exercise often involve mixed groups comprised of both men and women without considering age or the biological phase. Additionally, there is a lack of exploration of acute responses during the different MC phases. Although some studies have examined the influence of MC on symptomatology, as well as on disease progression and rhythm,^7^ to our knowledge, no studies have specifically determined the acute response to PA in females based on the hormonal profile derived from the MC phases. Therefore, studies exclusively focused on females with MS are essential to understand better the potential relationship between MC, PA practice and MS.^18^ Furthermore, the relationship between MS and females is a crucial aspect in the development of the disease, with the ovarian hormonal cycle being a sensitive stage, especially in females with RRMS.

Thus, the objectives of the study are: (a) to identify moderating variables that modify satisfaction with HIIT and strength training sessions throughout the MC in females with and without MS, and (b) to compare the acute effects of different types of PA sessions (HIIT and strength training) throughout the MC, in females with and without MS.

The central hypotheses of this study are the following: first, during the luteal phase of the MC, females with MS are expected to show a stronger association between inflammation and perception (fatigue and energy) and hormonal levels, as compared with females without the disease. Furthermore, HIIT and strength training sessions are expected to impact satisfaction with PA practice in both populations throughout the MC. During the luteal phase of the MC, females with MS are expected to exhibit different acute responses to HIIT and strength training sessions as compared with females without the disease.

## Material and methods

### Design

The present protocol describes the methodology of the EMMA Study, a randomised, single-blind crossover trial conducted on females with MS, matched 1:1 based on age, lifestyle factors (smoking, PA) and country of residence, with females without MS, to analyse the effect of PA practice (HIIT vs strength training) throughout the MC. To achieve this, the Consolidated Standards of Reporting Trials recommendations and protocols^19^ and previous studies that analysed the impact of the MC in females without MS^20^ will be followed. Participants will visit the facilities approximately 10 times (4 preliminary familiarisation visits and 6 visits to carry out HIIT and strength training session in each phase of the MC) over 3–4 months (figure 1).

**Figure 1 F1:**
[figure not shown]
Experimental design. EFP, early follicular phase; HIIT, high-intensity interval training; LFP, late follicular phase; MC, menstrual cycle; MLP, mid-luteal phase; MS, multiple sclerosis; post, immediately after exercise session.

### Participants

Females diagnosed with RRMS according to McDonald’s criteria^21^ and certified by their neurologist will be invited to participate in the study voluntarily. Recruitment will be carried out in collaboration with Regional Multiple Sclerosis Associations and hospitals in the provinces of Almería, Alicante, Jaén, Toledo and Murcia. The established inclusion and exclusion criteria will be analysed for all females who voluntarily express their interest in participating.

An a priori sample size estimate was performed using G*Power V.3.1 software (Heinrich-Heine-University, Düsseldorf, Germany) to estimate the number of females required for the study. An a priori sample size estimation was performed, setting the significance level at α=0.05, the power at β=0.95, a large effect size of f(v)=0.80 and a sphericity correction of 0.2 (1/repetitions−1). Additionally, a minimum dropout rate of 25% was considered following Hopkins *et al*’s recommendations.^22^ Since the study aims to analyse the effect of hormonal fluctuations, a previous study that analysed hormonal differences in females with regular cycles was used.^23^ A sample of 60 females (30 females without MS and 30 with MS) is necessary for the study. In the current study, the sample size is larger than in previous clinical trials that analysed the acute effects of PA on MS.^24^ Nevertheless, several studies have employed sample sizes ranging from 15 to 20 individuals with sclerosis and 15–20 without sclerosis. Therefore, the study will consider a minimum of 15 per control group.^25 26^

The inclusion criteria will be as follows: (a) women aged between 18 and 40 years old; (b) females with an MC length of ≥21 days and ≤35 days of natural menstruation; (c) absence of iron deficiency anaemia (serum ferritin >20 µg/L, haemoglobin >115 µg/L and transferrin saturation >16%); (d) being in a stable phase of the disease; and (e) to ambulate autonomously for more than 100 m. Participants will be excluded if they have: (a) a score <2 or >6 on the Expanded Disability Status Scale; (b) experienced a relapse in the 12 months before enrolment; (c) received corticosteroid treatment in the previous 2 months; (d) participated in a structured exercise programme in the past 6 months; (e) secondary amenorrhoea (absence of ≥3 consecutive periods despite not being pregnant and having previous menstruation); (f) used or currently using hormonal contraceptives for 3 months before recruitment; (g) reported musculoskeletal or neurological injuries not associated with MS, recent surgical interventions or pregnancies in the previous year; (h) diseases unrelated to MS. Furthermore, exercise and dietary restrictions and recommendations will be established 24 hours before the sessions, on the intervention day, and 24, 48 and 72 hours after, following the recommendations outlined in Peinado *et al*.^20^ Participants will be instructed not to modify their lifestyle during their participation in the project.

In addition to these inclusion and exclusion criteria, participants will be required to provide information, following the recommendations of Elliott-Sale *et al*,^27^ pertaining to the number of pregnancies (single or multiple pregnancies); age at menarche and any complications; previous MC irregularities; contraceptive use in the 12 months before the study, specifying the type (implants, injections, intrauterine devices/hormonal intrauterine systems, vaginal rings, transdermal patches) and formulation; the number of pregnancies resulting in gestational age of 24 weeks or more, regardless of whether the child was born alive or stillborn. Additionally, data on habitual PA (International Physical Activity Questionnaire), daily caffeine intake, dietary intake and nutritional supplements, alcohol consumption and smoking will be collected. Participants will also be asked to indicate the date of their MS diagnosis and the number of relapses.

Once all females with MS have been recruited, the enrolment of females without MS will begin, using a 1:1 matching methodology based on age, geographical area, lifestyle factors, and inclusion and exclusion criteria related to the MC. Before starting the study, all participants will read and sign an informed consent form. Furthermore, the project will adhere to the ethical principles of medical research involving human subjects described in the Declaration of Helsinki of the World Medical Association. This project and its procedures have also been registered in the US National Library of Medicine’s ClinicalTrials.gov database (NCT06105463).

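### The haemoglobin inclusion limit is printed in µg/L, so read literally this part of the anaemia screen excludes nobody; the unit needs correcting.

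*Protocol article*

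**What the plan says.** The Participants section lists the inclusion criteria. Criterion (c) requires "absence of iron deficiency anaemia" and then defines it in brackets by three limits: "serum ferritin >20 µg/L", followed by "haemoglobin >115 µg/L and transferrin saturation >16" (per cent). The limits are joined by 'and', so a participant must meet all three.

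The haemoglobin limit, "haemoglobin >115" µg/L, appears only here. No other section restates it or gives it in another unit. The same section says that the criteria will be examined for every woman who volunteers. Under Experimental procedures, eligibility is assessed at the first visit, where blood is also drawn.

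**The concern.** Micrograms per litre suits ferritin but not haemoglobin, which is present in blood in grams per litre. A limit of 115 µg/L lies so far below any human value that, taken as printed, it cannot separate anaemic from non-anaemic women.

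This is an eligibility rule that the trial applies, not background text. Fatigue on the VAS-F is one of the two primary outcomes, and the HIIT session uses intervals at 90% of peak power. The investigators evidently wanted anaemia screened out before taking such measurements. On the literal rule, a woman with low haemoglobin who passes the ferritin and transferrin saturation limits would meet criterion (c).

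**Working it through.** **Inputs**
- Haemoglobin limit as printed: 115 µg/L (Participants, inclusion criterion (c)).
- Companion limits in the same criterion: ferritin 20 µg/L and transferrin saturation 16%.
- Conversion: 1 g = 1,000,000 µg.
- Assumption, not in the documents: human haemoglobin lies between about 30 g/L (very severe anaemia) and 160 g/L.

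The limit is not derived from other figures in the article, so there is no calculation of the plan's own to reproduce. The check is a unit conversion.

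**Step 1. Put the printed limit on the g/L scale.**
115 µg/L ÷ 1,000,000 = 0.000115 g/L.

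**Step 2. Compare assumed haemoglobin values with the limit.**
Ratio = (haemoglobin in g/L × 1,000,000) ÷ 115.

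| Haemoglobin (g/L) | In µg/L | Ratio to printed limit | Passes? |
|---|---|---|---|
| 30 | 30,000,000 | about 261,000 | yes |
| 50 | 50,000,000 | about 435,000 | yes |
| 70 | 70,000,000 | about 609,000 | yes |
| 100 | 100,000,000 | about 870,000 | yes |
| 115 | 115,000,000 | 1,000,000 | yes |
| 120 | 120,000,000 | about 1,043,000 | yes |
| 160 | 160,000,000 | about 1,391,000 | yes |

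**Step 3. Read the result.**
Every value passes, so the conclusion does not depend on where in the assumed range a participant falls. The factor is exactly one million only at 115 g/L. For very severe anaemia (30 to 50 g/L) it is about 0.26 to 0.43 million.

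**Step 4. Consider where the unit came from.**
The ferritin limit stands immediately before the haemoglobin limit and carries the same unit, where it fits. A carried-over unit is the likely explanation. A fault in reading the PDF is unlikely: it might lose or garble a µ, but would hardly insert one.

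**The case against.** The best reply is that the slip largely corrects itself in use. The condition to be met is the absence of iron deficiency anaemia, and the figures stand in brackets after it. Anyone holding a real laboratory result beside the number 115 is unlikely to read it on a scale a million times smaller. That stands, and it is why the practical effect is probably small.

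A reader might go further and infer one of three things that the documents do not support.

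- *The whole anaemia screen is void.* It is not. Ferritin and transferrin saturation remain usable limits, and both bear directly on iron deficiency, which is the condition that criterion (c) names. A woman who passes both but has low haemoglobin more probably has another cause for it.
- *Anaemic women will be enrolled.* This does not follow. Exclusion (h), which rules out illness other than MS, could exclude a woman with known anaemia. Its wording is broad and its application is not spelled out, so the cover is partial. Nothing shows that staff would apply the haemoglobin limit literally.
- *The trial's inference is damaged.* The limit plays no part in the sample size, power or alpha. The comparisons between exercise types and between cycle phases are made within participants, so stable differences in haemoglobin between women matter less there. They could matter more for women with MS against women without, but the article gives nothing from which to estimate that effect.

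What remains after these replies is that the rule as printed is wrong and nothing else in the article corrects it. Recruitment runs through associations and hospitals in five provinces, and a published protocol may be copied. An eligibility limit should not depend on each reader repairing it silently.

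**Conclusion.** The point holds as a unit error in an operative eligibility limit. Read literally, the haemoglobin part of criterion (c) excludes nobody, because values across the assumed 30 to 160 g/L range exceed the printed limit by a factor of about 0.26 to 1.4 million. That range is an assumption, but any range on the scale of tens to hundreds of g/L gives the same conclusion.

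The consequence is confined to one of three joint limits and is probably small in practice. The case for correction is that a decision rule should be right as written and that the repair is cheap.

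**What to change.** The sponsor should check both the number and the unit of the haemoglobin limit against the source of criterion (c) and the unit in which the laboratory reports. It should then correct the Participants section and any screening document that repeats the limit; whether any does cannot be seen from the article. No new clinical threshold is proposed here, and which limit applies is for the sponsor to confirm.

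The cost is a short check and an edit to one criterion. The design, sample size and analysis need no change.

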**Figure 2 F2:**
[figure not shown]
A depiction of a 28-day menstrual cycle with ovulation on day 14, showing the typical fluctuations in ovarian hormones, such as oestrogen, progesterone and luteinising hormone (LH), as well as the changes in temperature, during the follicular and luteal phases. Modified from Peinado *et al*^20^ and Schmalenberger *et al.*^28^ Timing of sessions for an average duration cycle (28 days): from the first day of bleeding, the tests will be performed between the first and fifth day (EFP=low levels of sex hormones), between days 11 and 13 (LH peak or the same day; LFP=low levels of progesterone but high oestrogen levels), and between days 19 and 23 (after ovulation; MLP=elevated levels of both progesterone and oestrogen). EFP, early follicular phase; LFP, late follicular phase; MLP, mid-luteal phase.

During the 2–3 months before the intervention, familiarisation with the tests and PA sessions will be conducted. This familiarisation period will start with MC monitoring, allowing the appointment setting for/in each MC phase with little margin of error. For the monitoring of the MC and the setting of the appointments, the experimental considerations described below will be followed^27 29^:

Monitoring will be carried out starting 3 months before starting the intervention. Participants will be requested to provide information regarding the starting date of their six previous menstruations to estimate their MC duration. Then, during the two to three subsequent MCs, period starting dates will be collected concurrently with the familiarisation stage.Luteinising hormone (LH) peak detection urine kits will detect LH surge, ovulation, and, retrospectively, the LFP. This test will allow us to confirm that the MCs included in the study are ovulatory, as anovulatory cycles can occur even in normal cycles with regular menstruation.^29^In addition, serum hormone concentrations (see Reproductive hormonal profile subsection) will be measured for each training session retrospectively since this is a direct method and is considered the gold standard for research purposes.

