#### Randomisation

In this crossover study, the evaluation order will be counterbalanced according to the MC phases (EFP, LFP and MLP) using codes 1–3. Participants and their counterparts will undergo evaluations in different sequences: 1–2–3; 2–3–1; 3–1–2; 2–1–3; and 1–3–2.^20^ Additionally, the type of exercise (HIIT: 1 or strength training: 2) they will perform in each phase will be randomised. This randomisation approach will ensure an equitable distribution of the effects of the MC and the types of exercise among participants, contributing to obtaining more robust and reliable results for the analysis. The ‘OxMaR’ software will be used for the participant randomisation process.^30^

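### Enrolling controls only after the MS group is fully recruited aligns MS status with enrolment period, an avoidable risk mainly for between-group comparisons of outcome levels

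*Protocol article*

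**What the plan says.** The Participants section sets the recruitment sequence: "Once all females with MS have been recruited, the enrolment of females without MS will begin, using a 1:1 matching methodology". It lists the pairing factors as a "matching methodology based on age, geographical area, lifestyle factors, and inclusion and exclusion criteria related to the MC". The Design section gives a similar list (age, smoking, physical activity, country of residence). Neither includes date or season.

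The Randomisation section balances conditions within a woman. It says "the evaluation order will be counterbalanced according to the MC phases (EFP, LFP and MLP) using codes 1–3", and exercise type within each phase is randomised. Neither step can balance calendar time between women with and without MS.

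On timing, the Design section gives "4 preliminary familiarisation visits and 6 visits to carry out HIIT and strength training session in each phase of the MC) over 3–4 months", and the section on cycle monitoring says "Monitoring will be carried out starting 3 months before starting the intervention". No dates, wave lengths or testing schedule by group are given.

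The group comparison matters to the aims. Objective (b) in the Introduction compares acute effects of the two session types "in females with and without MS", and the third hypothesis, stated for the luteal phase, is that "females with MS are expected to exhibit different acute responses to HIIT and strength training sessions as compared with females without the disease".

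**The concern.** MS status cannot be randomised, so the MS versus non-MS contrast is observational even though the phase and exercise contrasts are controlled by design. In such a contrast, recruiting both groups over the same period is the simple protection against anything that changes with time. The stated rule gives that protection up: the whole control group enters after the whole MS group.

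Season (through habitual activity, sleep and outdoor heat) and growing staff experience could then differ between the groups for reasons unrelated to MS. Matching on age, area and lifestyle does not address this.

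Some of the outcomes extend beyond the climate-controlled room. Satisfaction and VAS-F are repeated at 24, 48 and 72 hours, and sleep is followed for three nights. VAS-F also asks about overall fatigue, not fatigue at one moment. A difference in the level of any of these could be read as an effect of MS when part of it reflects the period of testing.

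**Working it through.** The plan states no figure on this point, so there is none to reproduce. The check has three steps.

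**1. Is calendar time balanced anywhere?** Three mechanisms could do it.
- Matching: age, area, lifestyle and cycle criteria. No date.
- Randomisation and counterbalancing: phase order and exercise type within a woman. No date by group.
- Enrolment rule: MS group first, controls second. This creates the alignment.

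Nothing shown balances it.

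**2. Which comparisons are exposed?** Write an outcome as Y = group effect + period effect + occasion effect (pre, post, phase, exercise) + error. Let the later period shift the outcome by s SD, and let *a* be the difference between groups in the share tested in the later period (0 = same timing, 1 = no overlap).
- Group difference in level: true difference + *a*·s. Biased.
- Group difference in pre–post change: (post + shift) − (pre + shift) = post − pre, so a constant shift cancels.
- Group difference in a phase contrast or in HIIT versus strength: a shift constant over a woman's visits cancels in the same way.
- The last two are biased only if the period changes the response itself, for example if hot weather altered post-exercise fatigue in women with MS more than their pre-session level.

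**3. How large could the effect on a level comparison be?** Inputs:
- n per group: 15 (Abstract) or 30 (Participants section). The article gives both, so both are shown.
- α = 0.05 (Participants section), taken as two-sided.
- s = 0.2, 0.3, 0.5 SD: an assumption; the documents give no period effect.
- *a* = 1: an assumption, and the worst case.
- True MS effect = 0.

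Unpaired t-test: noncentrality λ = s·√(n/2), df = 2n − 2, critical value 2.048 (n = 15) or 2.002 (n = 30). Rejection rate = P(|t(df, λ)| > critical value).

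Paired t-test, with an assumed within-pair correlation ρ = 0.3: λ = s·√n / √(2(1 − ρ)) = s·√n / √1.4, df = n − 1.

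| n per group | s | λ unpaired | Rejects, unpaired | Rejects, paired (ρ = 0.3) |
|---|---|---|---|---|
| 15 | 0.2 | 0.2 × 2.739 = 0.548 | 8.3% | 9.4% |
| 15 | 0.3 | 0.3 × 2.739 = 0.822 | 12.5% | 15.0% |
| 15 | 0.5 | 0.5 × 2.739 = 1.369 | 26.2% | 33.2% |
| 30 | 0.2 | 0.2 × 3.873 = 0.775 | 11.9% | 14.6% |
| 30 | 0.3 | 0.3 × 3.873 = 1.162 | 20.8% | 26.9% |
| 30 | 0.5 | 0.5 × 3.873 = 1.936 | 47.8% | 60.9% |

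A larger sample makes the false-positive rate worse, because the bias stays while the standard error shrinks. Partial overlap scales the bias down: with *a* = 0.5 and s = 0.5 it is 0.5 × 0.5 = 0.25 SD, between the 0.2 and 0.3 rows. With pairs tested together *a* is about 0 and the rate returns to 5%.

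**The case against.** The strongest reply is that the rule governs recruitment, not testing. Monitoring begins three months before the intervention and visits run over 3–4 months, so late MS recruits may still be attending when controls enter. A reader might infer that the groups barely overlap and that no analysis could separate period from MS status. The article does not say so, and the degree of alignment is unknown. This stands. It is only partly reassuring, because controls have the same lead-in and the order of the groups is therefore preserved unless MS testing is held back.

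A reader might also infer that the groups fall in different assay batches. The article does not describe batching. Serum hormones are measured retrospectively, which leaves room for joint runs, and outcome detail is deferred to a supplement. No error can be claimed here, and the two self-reported primary outcomes involve no assay.

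It would likewise be too strong to say that every aim is a group contrast. Objective (a) seeks moderators of satisfaction, and the second hypothesis concerns effects in both populations. The third hypothesis is about acute responses, where a constant shift cancels.

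The Introduction does describe "a temporary worsening or exacerbation of neurological symptoms due to heat", but in connection with the rise in body temperature after ovulation, not with season. It makes a heat effect in MS plausible and does not show a seasonal one.

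Finally, several channels are controlled or measured: room climate, time of day, one trainer (stated in the strength section) and activity levels in each cycle. Completing the cases before matching controls is also a recognised approach. These points lower the likely size of s. They do not balance calendar time.

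**Conclusion.** The point holds in limited form. The enrolment rule aligns MS status with enrolment period, and nothing shown in matching or randomisation offsets this. Alignment with season and staff learning is possible, not documented.

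The exposure is mainly in between-group comparisons of levels. Under a fully aligned shift of 0.2–0.5 SD and no MS effect, an unpaired 5% test would reject in about 8–26% of trials (15 per group) or 12–48% (30 per group). Those figures illustrate an assumption about s and *a*. They are not estimates of this trial's error rate, and they do not apply to acute change, phase or exercise contrasts unless the period modifies the response. The within-woman comparisons of phase and of HIIT with strength training are not undermined by the rule.

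This is a cheap design improvement and not a must-fix error.

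**What to change.** Replace the sequential rule in the Participants section with rolling pair-wise enrolment. Start the search for each control when her MS counterpart is enrolled, and test both members of a pair close in calendar time. Individual 1:1 matching needs only the control's own case, so nothing in the matching requires the MS group to be complete first.

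Where samples are stored, assaying the two members of a pair together is a sensible addition. It does not correct anything the article states wrongly.

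The cost is protocol wording and recruitment logistics: control recruitment starts earlier, and an occasional control goes unused if her counterpart withdraws. No new procedures are needed, and the planned sample size does not change.
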